## Abstract

**Introduction::**

Acute cerebral infarction is a clinically common cerebrovascular disease. Acute cerebral infarction is characterized by sudden onset, dangerous illness, high risk of death, and disability. Computed tomography perfusion imaging can detect abnormal brain tissue perfusion 30 minutes after the onset of cerebral ischemia, providing the earliest and most valuable information for clinical diagnosis and treatment. In recent years, the effect of traditional Chinese medicine on acute cerebral infarction has been remarkable.

**Methods/design::**

This study plan randomly divided eligible acute cerebral infarction patients into two groups. Patients in the control group will be treated with conventional Western medicine; patients in the intervention group will be treated with traditional Chinese medicine cooperative therapy on the basis of conventional Western medicine. The curative effects will be selected before treatment, 2 weeks after treatment, and 3 months follow-up. The changes in CT imaging evaluation, NIHSS score, and BI index of the two groups of patients will be observed.

**Discussion::**

We aim to provide higher evidence-based medical evidence for traditional Chinese medicine treatment of acute cerebral infarction. And clarify the application value of computed tomography perfusion imaging in the diagnosis and efficacy evaluation of acute cerebral infarction.

**Trial registration::**

ClinicalTrials.gov, ChiCTR2000030230, Registered on 03 March 2020.

## Introduction

1

Acute cerebral infarction (ACI) is a clinically common cerebrovascular disease. ACI is characterized by sudden onset, dangerous illness, high risk of death, and disability.^[1]^ In recent years, the incidence of cerebrovascular disease has gradually increased. According to the WHO Global Disease Data Report, cerebral infarction is the third leading cause of death among residents worldwide, and it is also a major cause of disability.^[2,3]^ In recent years, the increase in the number of patients with acute cerebral infarction may be related to life, work, psychological stress, and incontinent diet. In addition, atherosclerosis and cardiogenic embolism are the two most common causes of cerebral infarction.^[4]^ The former can cause narrowing of the arterial lumen, leading to brain tissue necrosis. Another common cause of cerebral infarction is cardiogenic embolism. Most embolic emboli will stagnate on the head and cause ACI.

In terms of treatment, Western medicine has a greater limitation in the treatment of cerebral infarction.^[5]^ Western medicine treatment of cerebral infarction is mainly based on thrombolysis, antiplatelet aggregation drugs, and scavenging oxygen free radicals. The use of anti-platelet aggregation drugs is prone to bleeding, gastrointestinal reactions, liver and kidney damage, and is not suitable for patients to take for a long time. In addition, for the treatment of ACI, clinically, intravenous thrombolysis is often used to treat the disease.^[6]^ However, most patients have missed the thrombolytic time window when they were admitted to the hospital, or are unable to take thrombolytic therapy because of the uncertain onset time. With the continuous development of imaging diagnosis technology and equipment, the current ultra-early cerebral infarction diagnosis technology solutions available for clinical use are no longer limited to conventional computed tomography (CT) plain scans, and more and more new technical methods are being developed and utilized photon emission tomography, positron emission tomography, etc.^[7]^ However, the above-mentioned new diagnostic technology has not been popularized in primary medical institutions, and the medical burden is too heavy and the operation time is too long. The inability to complete the assessment of cerebral blood flow in emergency patients in a short time has become a difficult bottleneck for the development of this disease.^[8,9]^ Studies have found that CT perfusion imaging (CTPI) can detect abnormal brain tissue perfusion 30 minutes after the onset of cerebral ischemia, providing the earliest and most valuable information for clinical diagnosis and treatment. In recent years, the effect of traditional Chinese medicine (TCM) on ACI has been remarkable. Therefore, this study intends to use a clinical randomized controlled study to explore the exact effect of TCM in the treatment of acute cerebral infarction, and use CTPI imaging methods to evaluate the effect.

## Methods/design

2

### Study design and settings

2.1

A brief flowchart of the entire study is shown in Figure 1. We will perform a 2-group, randomized, single-blind, placebo-controlled, and multi-center trial that will evaluate the efficacy and safety of TCM cooperative therapy for patients with ACI. This study will use a completely random grouping and parallel control observation design method. We will ensure the balance of the baseline data of the two groups through a sufficient sample size and a completely randomized grouping method. The protocol includes elements recommended in the Standard Protocol Items: Recommendations for Interventional Trials checklist (Additional file 1).

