### Participants

2.2

All cases will be included in patients with acute stage of cerebral infarction admitted to the Department of Neurology, Dongzhimen Hospital. CTPI examination of the head will be completed. They will be randomly divided into two groups, the intervention group and the control group.

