#### Inclusion criteria

2.2.2

(1)Those who meet the ACI diagnostic criteria for Western medicine;(2)Those who meet the diagnostic criteria for stroke in Chinese medicine;(3)The time from onset to admission for treatment is within 72 hours;(4)The National Institutes of Health Stroke Scale (NIHSS) score is ≥6 points and ≤22 points;(5)Patients with first onset of ACI or patients with recurrent stroke have fully recovered before the onset of this disease;(6)Those who voluntarily accept the clinical observation of this project and sign the informed consent;

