### Randomization and blinding

2.6

The random method will use the closed envelope method. We will refer to the random number table to generate random arrangements for the intervention and control groups. The corresponding treatment serial number is sealed and placed in a light-tight envelope to form a random letter. Patients will be randomly assigned to the intervention group or the control group in the order of the included cases. In addition, at the time of drug distribution, all tested drugs must be accompanied by a corresponding numbered emergency letter before distribution. Medicines will be distributed according to the group and medicine number assigned to each patient's visit number. The number of the drug must remain the same during clinical observations.

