### Ethics

2.9

This study will be approved by the Ethics Committee of Dongzhimen Hospital Affiliated to Beijing University of Chinese Medicine. The study will be conducted under the Declaration of Helsinki principles, as well as following the norms of good clinical practice. Recruitment of patients has not started in this study. The study plan will be submitted to the ethics committee of the Ethics Committee of Dongzhimen Hospital Affiliated to Beijing University of Chinese Medicine for review. We will not start recruiting participants without the consent of the ethics committee.

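### Section 2.1 claims two properties the described design lacks: multi-center conduct, and baseline balance ensured by complete randomisation

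*Protocol article*

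**What the plan says.** Section 2.1 (Study design and settings) describes a "single-blind, placebo-controlled, and multi-center trial". It gives the allocation type as follows: "This study will use a completely random grouping and parallel control observation design method". It then makes a promise about the result: "We will ensure the balance of the baseline data of the two groups through a sufficient sample size and a completely randomized grouping method".

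Section 2.6 (Randomization and blinding) describes how the list is made: "We will refer to the random number table to generate random arrangements for the intervention and control groups". Assignments are sealed in opaque envelopes and used in sequence: "Patients will be randomly assigned to the intervention group or the control group in the order of the included cases". No block, stratum or minimisation factor is named.

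On location, section 2.2 (Participants) says that all cases will be patients "admitted to the Department of Neurology, Dongzhimen Hospital". Sections 2.3.2 and 2.4.1 name the same CT scanner with the same device number. Section 2.9 names one committee: "This study will be approved by the Ethics Committee of Dongzhimen Hospital Affiliated to Beijing University of Chinese Medicine".

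On the population, section 2.2.2 admits patients up to 72 hours from onset, with this severity range: "The National Institutes of Health Stroke Scale (NIHSS) score is ≥6 points and ≤22 points".

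On the analysis, section 2.7 names an independent-sample t test for general data, a paired t test for before and after, and one-way analysis of variance between groups. No covariate enters any of these.

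**The concern.** Two statements in section 2.1 describe the design as stronger than the rest of the article shows it to be.

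The first is the number of centres. A multi-center label tells the reader that the result was obtained across sites and that allocation was organised across them. Everything concrete in the article points to one hospital. If the label is wrong, it overstates generalisability. If it is right, recruitment, imaging and ethics are described incompletely, and a single list used in order of inclusion would not balance the arms within centres.

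The second is the word ensure. Randomisation makes the arms comparable in expectation; it does not fix the outcome of one draw. A larger sample shrinks chance differences without removing them. The promise also rests on a sample size that the visible text does not give, so a reader cannot check it. The between-group method named in section 2.7 uses no baseline information, so it gives up the usual way of recovering the precision that chance imbalance costs.

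**Working it through.** **Number of centres.** No arithmetic applies; the statements are set side by side.

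- Section 2.1: multi-center.
- Section 2.2: all cases from one neurology department of one hospital.
- Sections 2.3.2 and 2.4.1: one scanner, device number 73396 in both.
- Section 2.9: that hospital's ethics committee only.

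The first two cannot both be true. The scanner and the committee are supporting evidence, not proof, since one committee could act for several sites. No second site is mentioned anywhere.

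**Balance.** The article states no number of patients, power, effect size or SD in the visible text, so there is no figure of the plan to reproduce. Assumptions: totals N of 60, 100 and 200; 1:1 allocation; simple randomisation, which is the natural reading of sections 2.1 and 2.6.

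1. One continuous baseline covariate. In SD units, the difference between two arms of N/2 has standard error √(1/(N/2) + 1/(N/2)) = √(4/N) = 2/√N. The chance that it exceeds d in either direction is 2 × [1 − Φ(d√N/2)]. For d = 0.3:
   - N = 60: z = 0.3 × 7.746/2 = 1.162, chance 24.5%
   - N = 100: z = 0.3 × 10/2 = 1.500, chance 13.4%
   - N = 200: z = 0.3 × 14.142/2 = 2.121, chance 3.4%

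2. A lower threshold, d = 0.2, by the same formula: 43.9%, 31.7% and 15.7%. At N = 400 it is still 4.6%.

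3. At least one of five covariates beyond 0.2 SD, treating them as independent: 1 − (1 − p)^5. This gives 94.4%, 85.2% and 57.5% for N = 60, 100 and 200, and 20.8% at N = 400.

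4. Arm sizes, exact Binomial(N, 0.5): the chance of a split of 60:40 or worse is 15.5%, 5.7% and 0.6%. The cost of such a split is small: relative to equal arms, the variance of the difference rises by 1/(4 × 0.6 × 0.4) = 1.04, about 4%.

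**What imbalance does to the estimate.** If the covariate correlates r with the outcome, a baseline difference of 0.3 SD moves the unadjusted estimate in that trial by about 0.3r outcome SDs. Over repeated trials these shifts average to zero, and the ordinary standard error already includes them. Adjustment removes them and reduces the residual variance by a factor of about 1 − r². The documents give no r, so the gain cannot be put in numbers.

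These probabilities are in standardised units. They would be the same for narrow or wide entry criteria, so the NIHSS range of 6 to 22 and the 72-hour window do not raise them.

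**The case against.** The strongest reply is that simple randomisation is a sound design. It gives unbiased comparisons, and a two-sided 0.05 test already allows for chance imbalance. This stands. A reader might infer that a chance severity difference would bias the trial or invalidate its tests; the documents do not support that, and the loss is in precision and credibility.

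A reader might also infer that the allocation method has to be replaced. That does not follow either. Blocks in a single-blind trial make later assignments partly predictable, stratifying by NIHSS band leaves imbalance within bands, and a 60:40 split costs little. Statisticians could reasonably decline the change. Section 2.6 already provides opaque envelopes used in order of inclusion.

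Every N above is assumed. If the true size is large, the risk on any one covariate is modest: 3.4% beyond 0.3 SD at N = 200. The flow chart is not shown and may carry numbers, so the absence of a figure in the text should not be read as proof that no size was planned. NIHSS is also a secondary outcome; the documents quantify no link between it and the primary CT perfusion measures.

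Finally, covariate adjustment is commonly left to a statistical analysis plan, and a fuller protocol could specify blocks. The first part is fair as far as silence goes, but section 2.7 is not silent: it names the between-group method, and that method has no covariate. Block details in another document would contradict the completely random grouping stated here, so the article would still need correcting.

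None of this answers the conflict over centres or the word ensure.

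**Conclusion.** The point holds in a limited form. The multi-center label contradicts the single-department recruitment in section 2.2, and this is the firmest part. The statement that balance will be ensured is wrong for any sample size under complete randomisation; balance is expected on average, and how close one trial comes depends on an N that the visible text does not give. At assumed totals of 60, 100 and 200, the chance of a difference above 0.3 SD on one covariate is 24.5%, 13.4% and 3.4%, given 1:1 simple randomisation.

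The consequence is moderate. The comparison remains unbiased and its tests valid; what is lost is precision that baseline adjustment could recover, and credibility if a visible imbalance appears after balance was promised. The documents do not show that the trial needs a different allocation method.

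**What to change.** 1. Reconcile the number of centres. Either restate the trial as single-centre in section 2.1, or, if other sites will join, name them, correct sections 2.2, 2.3.2, 2.4.1 and 2.9, and stratify the allocation by centre.
2. In section 2.1, replace the promise to ensure balance with wording that complete randomisation is expected on average to balance the groups.
3. In section 2.7, replace the unadjusted between-group analysis of variance or t test for the outcomes with an analysis of covariance that adjusts for the baseline value of the outcome and for baseline NIHSS. For the NIHSS outcome these are the same covariate.

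Optional: permuted blocks of randomly varying size, stratified by NIHSS band. This needs a new allocation list and separate envelope sets, and brings some predictability.

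Cost: items 1 and 2 are wording if the trial is single-centre; a stratified list is needed only if sites are added. Item 3 needs no new data, since the CT measures are planned before treatment and NIHSS is needed for eligibility. The article says that recruitment has not started and ethics review is still to come, so all of this can be settled before the first patient is randomised.

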**Figure 1 F1:**
[figure not shown]
Study design flow chart.

### Participants

2.2

All cases will be included in patients with acute stage of cerebral infarction admitted to the Department of Neurology, Dongzhimen Hospital. CTPI examination of the head will be completed. They will be randomly divided into two groups, the intervention group and the control group.

#### Diagnostic criteria

2.2.1

The Western medicine diagnosis criteria of ACI will refer to the “*Guidelines for the Diagnosis and Treatment of Chinese Acute Ischemic Stroke*” revised by the Chinese Medical Association Neurology Branch in 2018. The diagnostic criteria are as follows:

(1)The patient has an acute onset.(2)Focal neurological deficits (numbness/weakness on one side of the limb, with or without speech impairment, etc.).(3)Responsible lesions or symptoms/signs appear on imaging for more than 24 hours.(4)Exclude non-vascular causes.(5)Brain CT/MRI excludes cerebral hemorrhage.

The diagnostic criteria of TCM will refer to the “*Stroke Diagnosis and Efficacy Evaluation Standards”*. The specific summary is as follows: (1) the main symptoms: ① hemiplegia; ② skewed tongue; ③ speech is astringent or unable to speak; ④ sensory function decline, disappearance, numbness. (2) Secondary symptoms: ① dizziness; ② upset and irritable; ③ stiff limbs; ④ sputum is sticky; ⑤ drinking water will cause coughing; ⑥ ataxia. Have more than 2 main symptoms, or 1 main symptom and 2 secondary symptoms, combined with the characteristics of acute onset, inducement, aura symptoms and imaging examination can confirm the diagnosis.

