#### Exclusion criteria

2.2.3

Patients will be excluded if they meet the following criteria:

(1)Large-scale cerebral infarction, the vital signs are not stable;(2)Transient ischemic attack or cerebral hemorrhage;(3)With severe heart, liver, lung, kidney, and hematopoietic system diseases;(4)Pregnancy or lactation period;(5)Mental abnormalities and the patient who cannot cooperate.

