#### Case rejection or shedding criteria

2.2.4

(1)Allergic reactions or serious adverse events occur.(2)In the course of clinical observation, the patient developed other diseases and did not meet the inclusion criteria.(3)Subjects have poor compliance (compliance with test drugs <80% or> 120%), or change medications automatically.(4)Cases in which blindness is disrupted midway for various reasons.(5)Patients and their families resolutely terminate the experiment.

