## Discussion

3

The early diagnosis of ACI is of great significance to improve the prognosis of patients and save patients’ lives.^[10]^ Because only when the condition is found and diagnosed early in the onset of cerebral infarction (within 6 hours) can subsequent treatment such as intravenous thrombolysis be advanced. In this way, we can grasp the optimal timing of thrombolysis and reduce the degree of brain tissue damage.^[11,12]^ In addition, it is clinically recognized that changes in cerebral blood flow can feed back pathological changes in human brain tissue.^[13]^ For example, cerebral hemodynamic changes in patients with cerebral infarction have obvious characteristics. It is mainly manifested in local neurochemical changes in the early stages of onset.^[14]^ In order to ensure the local normal blood supply, the cerebral blood vessels will inevitably show a state of compensatory expansion. Corresponding resistance to cerebrovascular circulation will be significantly reduced. Imaging showed increased cerebral blood flow and prolonged mean transit time of contrast medium.^[15]^ When the vasodilation reaches the upper limit, cerebral blood flow will decrease. Once the state persists for more than 6 hours, it means that the blood supply to the brain is greatly reduced. At this time, cerebrovascular dilatation reaches a decompensated state, which in turn causes irreversible damage. Some scholars have stated in research that comprehensively grasping the patient's brain imaging diagnostic information in the early stages of onset will help physicians to correctly judge the condition such as whether the central neuron is necrotic, whether there are penumbras in the surrounding area, and the area of the penumbra area is geometric.^[16,17]^ Take first aid measures symptomatically. It is not difficult to see that clarifying the lesions and their changes in cerebral blood flow is very important to reverse the outcome of brain tissue. And how to obtain more comprehensive and valuable information about blood flow in living cells has always been the focus of investigation in imaging medicine.

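### The 72-hour limit stops at admission, leaving onset-to-CTPI and onset-to-randomisation time without a stated upper bound, and the perfusion comparison does not adjust for time since onset

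*Protocol article*

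**What the plan says.** **Entry clock.** Section 2.2.2, criterion (3), reads "The time from onset to admission for treatment is within 72 hours". The clock starts at symptom onset and stops at admission.

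**Steps after admission.** Section 2.2 says of admitted patients that "CTPI examination of the head will be completed" and then describes random division into two groups. Section 2.6 assigns patients in order of inclusion. Neither section gives a time limit.

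**Outcome and analysis.** Section 2.4.1 makes CT perfusion parameters (CBF, CBV, MTT) the primary outcome. Section 2.7 names independent-sample t tests, paired t tests for before-after change and one-way ANOVA between groups. It names no covariate.

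**Time dependence.** The Discussion describes compensatory vasodilation with raised flow, then falling flow, and adds: "Once the state persists for more than 6 hours, it means that the blood supply to the brain is greatly reduced".

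**Diagnostic wording.** Section 2.2.1, criterion (3), reads "Responsible lesions or symptoms/signs appear on imaging for more than 24 hours". Section 2.2.2 makes the diagnosis an entry condition ("Those who meet the ACI diagnostic criteria for Western medicine"), and section 2.2.3 excludes "Transient ischemic attack or cerebral hemorrhage".

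**The concern.** By the article's own account, a perfusion value depends on how long after onset it is taken. The eligibility rule is the natural place to control that time, but it governs arrival at hospital, not the scan or the allocation. A patient admitted just inside 72 hours meets the criterion however long diagnosis, consent and scanning then take. The label of 72 hours therefore need not describe the patients actually scanned and treated.

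Patients at different stages then enter one comparison, and nothing in the named analysis removes the resulting spread. At stake are the precision of the primary comparison and a clear statement of whom the result applies to.

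A lesser matter is that diagnostic criterion (3) is garbled. Symptoms do not appear on imaging, and the sentence leaves open whether the 24 hours qualifies lesions, symptoms or both.

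**Working it through.** The article gives no sample size, standard deviation or delay figure to reproduce, so the check sets the rules side by side.

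**1. Upper bound on time to randomisation.** Let A be onset to admission, with A ≤ 72 h (section 2.2.2), and let x be admission to randomisation (no limit stated in sections 2.2 or 2.6). Then:

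onset to randomisation = A + x ≤ 72 + x

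The article does not give x, so these values are assumptions:

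| Assumed x (h) | Latest onset-to-randomisation (h) |
|---|---|
| 6 | 72 + 6 = 78 |
| 24 | 72 + 24 = 96 |
| 48 | 72 + 48 = 120 |

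The same form holds for the baseline CTPI, with x read as admission to scan. Late scans are permitted by the text but not shown to occur.

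**2. Does time matter for this outcome?** The Discussion describes flow first raised and later reduced, with a change of state at about 6 hours. Perfusion is thus stated to vary with time since onset, and not in a straight line. Most of the described change lies early, inside the 72 hours. Moving the end of the window therefore trims only the late tail, and a covariate is needed for the spread within the window.

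**3. Does the named analysis absorb it?** With two groups, one-way ANOVA is the two-sample t test (F = t²). Neither adjusts for baseline perfusion or for onset time. If those two variables together explain a fraction R² of the outcome variance within arms, adjustment reduces the residual variance to about (1 − R²) of its unadjusted value. The article gives no basis for R², so the gain cannot be put in figures.

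**4. Is the comparison biased?** Section 2.2 places CTPI before random division, so the onset-to-scan delay has arisen before allocation. Its expected distribution is the same in both arms. What remains is added variance and chance imbalance.

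**5. The two readings of diagnostic criterion (3).**
- *Lesion on imaging, or symptoms for more than 24 h.* A patient with a visible responsible lesion can qualify at any hour. Only a patient without one waits past 24 h.
- *The 24 h applies to both.* An arrival at hour 2 waits 24 − 2 = 22 h. That patient still meets inclusion (3), because its clock stopped at admission. The two rules overlap for 72 − 24 = 48 h.

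Neither reading makes the rules incompatible. The sentence needs clarifying, and nothing more follows from it.

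**The case against.** **The limit may exist elsewhere.** This is a condensed article, the schedule figure is not shown, and the full protocol may cap the time to scan or randomisation. The words about admission for treatment might also be meant as the start of treatment. Both are possible and soften the point. Even so, the article does state an entry clock, and as written it ends at admission; if the start of treatment is meant, the wording should say so.

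**The consequence is limited.** The delay precedes allocation, so the arms are not systematically different, and covariate choice is often left to an analysis plan. The first part stands in full. The second stands in part, but section 2.7 does name its tests, and they are unadjusted.

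**Stronger inferences that the documents do not support.** A reader might infer from the 24-hour wording that early arrivals cannot qualify, that the first 6 or 24 hours are shut out, or that the 24-hour and 72-hour rules contradict each other. The word joining lesions and symptoms offers two routes, and on the workable reading a visible lesion suffices at once. Even on the most literal reading, early arrivals are delayed, not barred. Nor does the Introduction's remark that CTPI "can detect abnormal brain tissue perfusion 30 minutes after the onset of cerebral ischemia" make the earliest hours essential: it describes what the technique can detect, while the trial admits patients up to 72 hours.

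**Conclusion.** The point holds as a gap in definition and an avoidable loss of precision. Nothing in the article bounds onset-to-CTPI or onset-to-randomisation time, and the named analysis ignores a source of variation that the Discussion itself describes. The comparison between arms is not systematically biased.

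The size cannot be stated. The 78, 96 and 120 hours rest on assumed delays, and the loss of precision depends on an R² that the article does not give. The conclusion assumes that admission means arrival at hospital, that no unshown document sets the limit, and that the baseline scan precedes randomisation, as the order in section 2.2 implies. The wording of diagnostic criterion (3) is a minor clarification only.

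**What to change.** 1. **Inclusion criterion (3):** let the 72 hours run from onset to randomisation, and require the baseline CTPI inside that window and before allocation.
2. **Case report form:** record onset-to-CTPI time. It follows from the onset time already needed for eligibility and the scanner's time stamp.
3. **Section 2.7:** for the between-group CTPI comparison, use a linear model with treatment arm, baseline perfusion value and onset-to-CTPI time. Fix the functional form of time in advance and allow for curvature, since the Discussion describes a rise and then a fall.
4. **Diagnostic criterion (3):** reconcile the wording with the 2018 guideline that section 2.2.1 refers to, so that it is clear whether the 24 hours applies to lesions, symptoms or both.

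Section 2.4.1 also speaks of CTPI in patients whose onset time is unknown. Neither the 72-hour rule nor the covariate can be computed for them until onset is defined, so that sentence needs reconciling with inclusion (3).

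The cost is two reworded criteria, one derived time and one model. Recruitment had not started when the article was submitted. The downside is that a few patients admitted close to 72 hours would be lost.
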